#### Secondary outcomes

Serum oxidised LDL is the secondary outcome of the current study and will be analysed by enzyme-linked immunosorbent assay (ELISA). Optical density will be measured using an electronic plate reader and can be used to determine the quantity of the specific antigen in the blood using a calibration curve.

ELISA will also be used for quantitative analysis of C-reactive protein, neopterin, TBARS, fasting insulin and sex hormone binding globulin (SHBG). Free testosterone will be measured using a liquid chromatography method. This method has been chosen due to its ability to detect small amounts of serum testosterone, particularly in lower concentrations in females [20]. Free testosterone will be quantified using a calibration curve and calculating peak area.

Aerobic fitness will be assessed using the Astrand-Rhyming test. This is a submaximal single-stage test performed on a cycle ergometer, lasting between 6 and 7 min [21]. The goal is to obtain heart-rate values between 125 and 170 beats per minute (bpm) for a given work-rate at 50 revs/minute (50 or 75 watts for unconditioned women) [21]. Heart rate is then measured at the fifth and sixth minute if steady state (a difference ≤ 5 bpm is achieved), and the average of the two heart-rate measurements can be used to estimate VO_2max_ according to a nomogram. This value must be adjusted for age to account for decreasing maximal oxygen uptake and maximal heart rate with age [19].

For lipid profile (including LDL-cholesterol, HDL-cholesterol, TG and TC) and fasting glucose, a Cholestech Automated Analyser will be used. A fingerprick blood sample is obtained and collected into a capillary tube. The sample is then inserted into the machine cassette. This produces an automated reading from the sample in which accuracy can be maintained by using control samples and calibrations. HDL sub-fractions will be measured using gel electrophoresis.

In order to measure the amount of lifestyle physical activity (and subsequent sedentary activity), the long-form International Physical Activity Questionnaire (IPAQ) will be administered at baseline and post-intervention to all participants. This will be used to compare differences in time spent sitting, both during the week and weekend, and the amount of lifestyle physical activity (including transport, housework, and leisure time) undertaken.

Waist circumference will be measured with the participant standing with feet together, and the tape measure placed around the narrowest part of the torso, between the umbilicus and the xyphoid process [19]. Hip circumference will be measured with the participant standing as above, and the tape measure placed around the maximum circumference of the buttocks [19].

### Blood sampling and storage

Blood will be drawn from participants on their initial and post-intervention visit to the CSES, by a member of the research team trained in venepuncture. Blood samples will be centrifuged and serum aliquoted and stored at − 80 °C until they are analysed.

Assays will be performed at the Biomolecular Research Centre, Sheffield Hallam University, by a member of the research team.

### Data collection, monitoring, management and storage

Data will be collected by the chief investigator (AW) using data collection forms and entered into a computerised database. Range checks will be carried out to ensure data quality. Data checks will frequently be completed by other members of the research team.

Participants’ names will be anonymised and replaced with a code using a computerised pseudonymisation programme (Open Pseudonymiser, University of Nottingham, UK). All other study data will be stored securely on Sheffield Hallam University premises and/or saved on encrypted computer drives on site. Only the research team will have access to the data, including the final trial dataset. Data will be securely archived after study closure and stored for up to 7 years, when it will be destroyed. All data will be stored and managed according to Sheffield Hallam University’s confidentiality and data protection policies.

Due to the low risk involved in this study, no formal data monitoring committee will be formed. However, the study will be regularly monitored by the research team members being led by a senior team member (MK) who will meet at regular intervals throughout the study period.

### Interview and qualitative methods

After trial completion, four participants from each group, as well as drop-outs, will be offered the opportunity to complete a semi-structured interview either in person or over the telephone with a member of the research team. All interviews will be recorded with an audio recording device and then transcribed verbatim. The interview will explore their opinions and experiences of the intervention, and factors that may be a barrier or facilitator to physical activity in the future. It will also assess the acceptability of the exercise intervention and study procedures, to refine the design and delivery of the exercise programme for the RCT, and will last approximately 45 min.

Interviews will allow the exploration of participant’s motivations, attitudes and experience in detail and within their personal frame of reference. This will be useful because of the wide-ranging symptoms of PCOS, which may affect individuals in a variety of ways that are not necessarily uniform across all participants. Transcripts will be analysed using thematic analysis [22]. Thematic analysis is an inductive method for identifying, analysing and reporting patterns within data. As such, it allows for a great deal of flexibility in analysing qualitative data because it is independent of theory and epistemology; rather, it can be applied across a range of theoretical approaches [22]. This allows for themes and patterns to be identified by the researcher without trying to fit it into a pre-existing coding frame, and is therefore considered to be data-driven and accessible [22].

### Data analysis

All quantitative measurements will be presented as mean ± standard deviation (SD) unless otherwise stated.

As this is a feasibility study, no formal sample size calculation was required. The sample size for a feasibility study needs to strike a balance where it does not cause undue burden on participants by being too large, but not be too small that critical parameters (such as consent rate, attrition, and compliance) cannot be precisely estimated and used for the calculation of a full-scale RCT. It has been posited that a rule of thumb of at least 30 participants overall should be sufficient for a feasibility trial [23].

Additionally, sample sizes between 24 and 50 have been recommended to calculate a standard deviation of an outcome that can then be entered into a formal power calculation for the full-scale RCT [24, 25]. Oxidised LDL concentrations are a secondary outcome for the proposed study, and a sample size within this remit will provide a reliable standard deviation for oxidised LDL to be used in a power calculation. Since there are three groups, a total sample size of 51 will allow even numbers across three groups (17 in each group).

Descriptive statistics will be used to characterise the groups at baseline and post-intervention. Pre and post-intervention means will be recorded for each group. Difference between means will be assessed using two-factor mixed-ANOVAs where the effect of two independent variables (grouping and time point) will be measured on the dependent variables. The within-subjects factor is time, and the between-subjects factor is group. Post-hoc analysis will be undertaken in the event of any significant differences in group means. Data will be assessed to ensure the assumptions of the mixed-ANOVA are met including checks for normality.

Using free-testosterone data, all participants will be categorised by androgen profile as normo-androgenic or hyper-androgenic based on laboratory cut-off values [26]. Androgen profile will then be added into the mixed-ANOVA model, where time and androgen profile will be the within-subjects factors and group will be the between-subject factor. Partial eta squared will be presented. Assuming normality, Pearson correlation coefficient will be used to analyse the bivariate correlation between variables. Results of all analyses will be interpreted with a caveat that the study is a feasibility trial without a formal sample size calculation and as such may be inadequately powered. All statistical analysis will be undertaken using the latest IBM SPSS Statistics software, currently version 24.0.

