## Methods/design

### Study design

This study is a feasibility study involving an exploratory RCT. Fifty-one adult females with PCOS who are aged 18 years or over and pre-menopausal will be randomly assigned to a 12-week exercise intervention, an increased lifestyle physical activity group, or a control group. Outcomes will be measured pre- and post- intervention. Interview sessions will be undertaken with a proportion of participants at the end of the trial to provide qualitative information regarding barriers and facilitators to increased physical activity. The study is being conducted at the Centre for Sport and Exercise Science (CSES), Sheffield Hallam University, Sheffield, UK. Sheffield Teaching Hospitals, Sheffield, UK, will be used as a participant recruitment centre.

The study duration is from September 2018 up to May 2021 and is sponsored by CSES, Sheffield Hallam University.

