### Withdrawals

Participants may withdraw at any time without providing a reason. They may also choose to withdraw their data from the study. A participant will be considered to be withdrawn if they request to leave the trial or they are lost to follow-up. If allocated to the exercise group, participants will be considered as withdrawn if they no longer attend the supervised exercise sessions, and in the lifestyle physical activity group if they no longer monitor daily physical activity through the fitness application. Data from withdrawn participants will not be used; only data from participants who completed the intervention and baseline and post-intervention assessments will be used in analysis.

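### The post-hoc gate is worded on group means and group-by-time is never named; a baseline-adjusted 12-week comparison would be clearer and more precise

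*Protocol article*

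**What the plan says.** Under Study design, the protocol states that "Outcomes will be measured pre- and post- intervention", so there are two time points. Under Data analysis, it plans "two-factor mixed-ANOVAs where the effect of two independent variables (grouping and time point) will be measured on the dependent variables" and then assigns the factors: "The within-subjects factor is time, and the between-subjects factor is group". The rule for going further is that "Post-hoc analysis will be undertaken in the event of any significant differences in group means".

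The same section commits to recording pre and post means for each group. It adds androgen profile to the model and promises partial eta squared, without saying for which term. The group-by-time interaction is not named anywhere, and no baseline covariate is mentioned.

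On status, "Oxidised LDL concentrations are a secondary outcome for the proposed study"; feasibility and acceptability are primary. On size, "As this is a feasibility study, no formal sample size calculation was required", and all results are to carry a caveat about power. The Discussion nevertheless says that the study should supply effect sizes for planning a full-scale RCT.

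**The concern.** With one measurement before and one after randomisation, the two effects that the section describes are not the ones that answer the trial's question. The time effect pools all arms and involves no randomised comparison. The group main effect averages a baseline, which cannot contain an intervention effect, with the post value. The randomised comparison lies in the group-by-time term or in a baseline-adjusted difference at 12 weeks.

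An analyst who takes the post-hoc sentence literally could therefore run pairwise comparisons only when the group main effect is significant, and could report partial eta squared for that term. A real effect would usually fail that gate, and the effect size passed on to the full-scale trial would be too small. Even on the better reading, the two active-versus-control differences are formally compared only after a significant omnibus result, and by a method less precise than the baseline data allow.

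**Working it through.** **The plan's own figure.** 3 groups × 17 = 51, as stated. The protocol gives no alpha, power, effect size, SD or dropout rate, so nothing else can be reproduced.

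**Inputs.** From the protocol: three equal groups of 17 and two time points. Assumed, because the protocol gives none of them: alpha 0.05, equal true baseline means, SD 1 at both times, pre/post correlation ρ, and post-intervention shifts δ in SD units.

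**What each test sees.**
- Group main effect (each person's mean of pre and post): shift δ/2, variance (1+ρ)/2.
- Group-by-time (with two time points, identical to ANOVA on change): shift δ, variance 2(1−ρ).
- ANCOVA (post value adjusted for baseline): shift δ, variance 1−ρ².

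The noncentrality is λ = 17 × Σ(shift − mean shift)² / variance. The F test has 2 numerator degrees of freedom and 48 denominator degrees of freedom (47 for ANCOVA).

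**Scenario A: shifts 0.8, 0.4 and 0.** 17 × (0.4² + 0² + 0.4²) = 5.44, and with halved shifts 5.44/4 = 1.36.

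| ρ | λ main | λ group-by-time | λ ANCOVA | Rejection: main / group-by-time / ANCOVA |
|---|---|---|---|---|
| 0.5 | 1.36/0.75 = 1.81 | 5.44/1.00 = 5.44 | 5.44/0.75 = 7.25 | 0.20 / 0.51 / 0.64 |
| 0.6 | 1.36/0.80 = 1.70 | 5.44/0.80 = 6.80 | 5.44/0.64 = 8.50 | 0.19 / 0.61 / 0.72 |
| 0.7 | 1.36/0.85 = 1.60 | 5.44/0.60 = 9.07 | 5.44/0.51 = 10.67 | 0.18 / 0.75 / 0.82 |

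The ratio of main-effect to group-by-time noncentrality is (1−ρ)/(1+ρ), which is 0.25 at ρ = 0.6.

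**Scenario B: both active arms shifted by 0.8, wider range of ρ.**

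| ρ | Main | Group-by-time | ANCOVA |
|---|---|---|---|
| 0.3 | 0.29 | 0.49 | 0.69 |
| 0.5 | 0.25 | 0.64 | 0.77 |
| 0.7 | 0.23 | 0.86 | 0.92 |
| 0.8 | 0.22 | 0.97 | 0.98 |

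A simulation of 20,000 replicates agrees, with ANCOVA slightly lower than the formula (for example 0.76 against 0.77 at ρ = 0.5). The Withdrawals section says that "only data from participants who completed the intervention and baseline and post-intervention assessments will be used in analysis", so the analysed groups may be smaller than 17. With 14 per group (assumed), the scenario B ranges over ρ 0.3 to 0.8 become 0.18-0.24 for the main effect and 0.41-0.93 for group-by-time.

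**Change score against ANCOVA.** The variance ratio is 2(1−ρ)/(1−ρ²) = 2/(1+ρ): 1.54 at ρ = 0.3, 1.33 at 0.5, 1.25 at 0.6, 1.18 at 0.7 and 1.11 at 0.8.

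**Type I error.** In the same simulation with no effect, all three tests reject in 4.7% to 5.3% of replicates. With one arm's baseline mean set 0.5 SD high and no intervention effect, the main-effect test rejects in 4.9% (ρ = 0.3) falling to 1.4% (ρ = 0.8).

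**The case against.** A reader might infer that the plan tests the wrong contrast. The text does not establish that. A mixed ANOVA with group and time ordinarily contains their interaction, and nothing in the protocol excludes it. The sentence on post-hoc tests follows one that records pre and post means for each group, so the means it refers to may be those cell means; the section does not speak of a main effect of group. The 18-20% figure depends on the other reading.

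Nor does the plan ignore the baseline if the interaction is tested. A change-score analysis uses it and is valid under randomisation, so the case for ANCOVA is one of precision.

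The consequences are also limited. These outcomes are secondary, the sample size rests on no power calculation, and low power is already acknowledged. Group means and SDs are reported without any gate, so unadjusted 12-week differences could be worked out from them. The aim of obtaining an SD for oxidised LDL does not depend on the post-hoc rule. Much of the detail on terms and contrasts could properly sit in an analysis plan that is not shown.

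All of this stands. What remains is that the protocol does state a decision rule, that its wording points at least as readily to the uninformative term as to the informative one, and that partial eta squared is left without a term although effect sizes are to be carried forward. Pre and post means and SDs alone also do not yield a baseline-adjusted difference with its interval.

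**Conclusion.** The point holds as a matter of clarity and efficiency. It is not a mandatory correction.

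- If the gate is the group main effect, it sees half of any intervention effect and would miss most real ones: about 18-20% rejection against 51-75% for group-by-time in scenario A.
- If the gate is group-by-time, the analysis is sound, but its variance is 1.33, 1.25 or 1.18 times that of ANCOVA at ρ = 0.5, 0.6 or 0.7.

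The protocol does not say which applies. The figures rest on the assumed alpha, shifts and correlations, equal variances and all 51 participants analysed; completer-only analysis may reduce the numbers.

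A reader might also infer that chance baseline imbalance makes the gate open falsely too often. The check does not support this: unconditional type I error is about 5% for all three tests, and the half-SD imbalance examined did not raise the main-effect rejection rate above that. The practical stake is the quality of the effect sizes handed to the full-scale RCT. The primary feasibility outcomes are unaffected.

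**What to change.** For each continuous secondary outcome, fit the post-intervention value on the baseline value and group. Report the adjusted exercise-control and lifestyle-control differences with 95% confidence intervals whatever the omnibus result.

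If the mixed ANOVA is kept, state that group-by-time is the test of intervention effect, make post-hoc comparisons depend on that term, and report partial eta squared for it.

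The cost is a change of wording and one degree of freedom for the baseline covariate. No new data are needed, since baseline values are already collected, and N stays 51.

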**Methods/design:**

A feasibility, exploratory RCT will be conducted. Fifty-one pre-menopausal females will be randomly allocated between an exercise group (EG), a lifestyle physical activity group (LPAG) and a control group. Participants in the EG will undertake a 12-week supervised aerobic exercise programme. The LPAG will aim to increase daily physical activity and reduce sedentary behaviour for 12 weeks. The control group will not take part in any intervention. Primary outcomes are feasibility and acceptability of the intervention and procedures. Secondary outcomes are oxidised LDL, aerobic fitness, blood lipid profile, fasting glucose and insulin, testosterone and inflammatory markers.

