### Baseline and post-intervention measurements

During visit 1, after written informed consent has been obtained and eligibility confirmed by AW, the following baseline tests measurements will be made: age, anthropometric measures (stature, body mass, hip and waist measurements), finger-prick and venous blood sampling (see Outcome measures for a detailed description of analytes), aerobic fitness assessed by the Astrand-Rhyming single stage test (see Outcome measures for detailed description).

After completion of the intervention, all tests and measurements will be repeated.

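### Free testosterone defines the androgen class and is not excluded from the model partitioned by that class; if the class is set at baseline, regression to the mean would bias the androgen-by-time term for that one outcome

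*Protocol article*

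**What the plan says.** All references are to the protocol article.

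- **Classifier.** Data analysis: "Using free-testosterone data, all participants will be categorised by androgen profile as normo-androgenic or hyper-androgenic based on laboratory cut-off values". The section does not say whether the baseline sample, the post-intervention sample or both supply the value.
- **Outcome.** Abstract, Methods/design: "Secondary outcomes are oxidised LDL, aerobic fitness, blood lipid profile, fasting glucose and insulin, testosterone and inflammatory markers". The assay is described under Secondary outcomes: "Free testosterone will be measured using a liquid chromatography method".
- **Sampling.** Blood sampling and storage: "Blood will be drawn from participants on their initial and post-intervention visit to the CSES". Baseline and post-intervention measurements: "After completion of the intervention, all tests and measurements will be repeated". No separate sample for classification is described.
- **Base model.** Data analysis specifies a group-by-time mixed ANOVA, "where the effect of two independent variables (grouping and time point) will be measured on the dependent variables". No dependent variable is listed and none is excluded.
- **Partitioned model.** Data analysis continues: "Androgen profile will then be added into the mixed-ANOVA model, where time and androgen profile will be the within-subjects factors", with group as the between-subjects factor.
- **Purpose.** Finding out whether partitioning by androgen profile is useful is one of the specific aims in the Background. The Discussion describes its purpose in terms of cardiometabolic profiles and how exercise and activity affect them.
- **Caveat.** The only caution attached to these analyses is that power may be inadequate.

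**The concern.** A woman above a laboratory cut-off on a single sample is there partly because of her usual level and partly because of assay error and day-to-day variation. On a second sample the transient part does not recur. Women classed as hyper-androgenic therefore tend to fall and women classed as normo-androgenic tend to rise, in every arm and without any intervention effect. When the outcome is free testosterone itself, the model reads this as an androgen-by-time interaction.

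At stake is how one secondary result is read. A fall in testosterone among hyper-androgenic women, reported with a partial eta squared, could be taken as evidence that partitioning is informative, and partitioning is something the study sets out to assess. The low-power caveat does not help: it warns of missed effects, whereas this is a false positive.

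The same sentence has a second fault. It makes androgen profile a within-subjects factor, but one label per woman does not vary within a woman.

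**Working it through.** **Inputs from the document.** Sample size: 3 arms × 17 = 51, which reproduces the stated total. The article gives no alpha, effect size, SD or power for these tests, so there is no other figure to reproduce. Analysis is restricted to completers, with no dropout rate stated.

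**Assumptions not in the document.** Pre-post correlation of free testosterone ρ from 0.5 to 0.95; share classed hyper-androgenic q of 0.5 or 0.7; two-sided alpha 0.05; bivariate-normal values in SD units; no change over time and no intervention effect; class set from the analysed baseline value; 42 completers as an illustration of dropout.

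**Expected artefact.** Let X₁ and X₂ be the standardised pre and post values and c the cut-off.

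- E[X₂ − X₁ | X₁] = −(1 − ρ)X₁
- E[X₁ | X₁ > c] = φ(c)/q and E[X₁ | X₁ ≤ c] = −φ(c)/(1 − q)
- Hyper-minus-normo difference in change = −(1 − ρ) × φ(c) / [q(1 − q)]

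At ρ = 0.7 and q = 0.5, φ(0) = 0.399, giving −0.3 × 0.399 / 0.25 = −0.48 SD: a fall of 0.24 SD in one class and a rise of 0.24 SD in the other.

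**False-positive rate.** With two time points, the androgen-by-time test is a test of androgen class in a regression of change on group and androgen class. The class is entered as a between-subjects factor, because the within-subjects label in the protocol cannot be fitted with one label per woman. Simulation with 2,000 runs per setting gave:

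| ρ | Spurious difference, q = 0.5 (SD) | Rate, n = 51, q = 0.5 | Rate, n = 51, q = 0.7 | Rate, n = 42, q = 0.5 |
|---|---|---|---|---|
| 0.5 | −0.80 | 84% | 81% | 76% |
| 0.6 | −0.64 | 72% | 68% | 63% |
| 0.7 | −0.48 | 59% | 55% | 50% |
| 0.8 | −0.32 | 42% | 39% | 35% |
| 0.9 | −0.16 | 24% | 20% | 20% |
| 0.95 | −0.08 | 14% | 13% | 12% |

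**Where the bias does and does not reach.**

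- Group-by-time-by-androgen for free testosterone: about 4–6% in every setting. Randomisation makes the regression to the mean the same, on average, in each arm. The group-by-time comparison is unbiased for the same reason.
- Another outcome whose visit-to-visit error is independent of testosterone's, with the class still set at baseline: about 5%.
- Class set from an independent sample, or from the mean of the two samples: about 4–6%, with a spurious difference near zero. The mean is shown only to locate the source of the bias; it would build post-intervention data into the class.

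**The case against.** The strongest objection is that two premises are inferred. No sentence says free testosterone is run in the partitioned model; this follows only from an unrestricted reference to the dependent variables, and the Discussion gives cardiometabolic profiles as the purpose. Nor does any sentence say the class comes from baseline. Both points stand. A reader might infer that the artefact is certain; the document does not support that. A class taken from the average of both samples would not show it. A class taken from the post-intervention sample would show it in mirror image and could itself be altered by the intervention. A class reassigned at each visit, which the within-subjects label might suggest, would be circular in another way.

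A reader might also infer that the comparison of exercise or activity with control, or the finding on how androgen profile modifies it, is compromised. It is not. The Discussion's question about the effect of exercise and activity by androgen profile is answered by the three-way term, which keeps its nominal error rate. Nor does the artefact as such extend to oxidised LDL, lipids or fitness. It would reach another outcome only if that outcome's visit-to-visit error were correlated with testosterone's.

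It can further be said that the rates depend on a correlation and a split that the article does not give, that laboratory cut-offs need not fall at the median, and that the trial's primary outcomes are feasibility and acceptability. All true, and these limit the weight of the point. They do not remove it: even at a correlation of 0.95 the rate is more than double the nominal 5%. It would also be too strong to call any observed interaction pure artefact, since a biased estimate can still contain real change.

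**Conclusion.** The point holds conditionally and is narrow. As written, the Data analysis section lets free testosterone be analysed by a class cut from free testosterone. If that class comes from the analysed baseline sample, the androgen-by-time term for that outcome is biased by regression to the mean. With no true change, n = 51 and a 50% split, the false-positive rate at nominal 5% runs from about 84% (correlation 0.5) to 14% (correlation 0.95); with a 70% split, from about 81% to 13%. These figures rest on the assumed correlation and split, normality and classification at baseline.

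Group-by-time, group-by-time-by-androgen, and outcomes with visit-to-visit error independent of testosterone's are not biased by this. Describing androgen profile as a within-subjects factor is an error in the same sentence and needs correcting alongside it.

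**What to change.** In the Data analysis section:

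1. State that androgen class is set from the baseline sample only.
2. Enter androgen class as a between-subjects factor alongside group, leaving time as the only within-subjects factor.
3. State that the androgen-partitioned model is not fitted to free testosterone, which is analysed by group and time only.
4. Judge whether partitioning is useful on outcomes that do not define the class: oxidised LDL, lipids, insulin, glucose and fitness.

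Comparing arms on post-intervention free testosterone with continuous baseline free testosterone as a covariate is an optional gain in precision. It is not needed to remove this bias, because the comparison between arms is not affected by it.

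The cost is a few sentences of analysis wording and the loss of one set of androgen-partitioned results. No new data are needed.

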## Discussion

Oxidised LDL has been associated with all stages of atherosclerosis, as well as other conditions linked to CVD, such as diabetes mellitus and metabolic syndrome [27]. PCOS is associated with various increased risk factors for CVD, including hypertension, dyslipidemia, abdominal obesity, insulin resistance, inflammation, and endothelial dysfunction [3, 6]. Whether oxidised LDL has a role in this increased risk in PCOS is not yet known.

The present study aims to measure the feasibility of implementing exercise training and/or a lifestyle physical activity intervention in women with PCOS. This will provide necessary information to design an adequately powered RCT examining the effect of such interventions on oxidised LDL and CVD risk. The strengths of this study include the lifestyle physical activity arm, which will encourage participants to be more active whilst reducing time spent sedentary, and monitor their daily physical activity, so that the effects of this can be compared with a formal, structured exercise programme. Additionally, partitioning data by androgen profile will highlight differences in normo- and hyper-androgenic cardiometabolic profiles and how exercise and physical activity can impact these. This study aims to provide feasibility data and effect sizes in order to plan for a full-scale RCT. In addition, it aims to contribute to recommendations that move away from a one-size fits all approach to PCOS management and move to recommendations based on individual presentations of the condition. A limitation is that some self-monitoring in the lifestyle physical activity group may not be reliable or replicable, for example inputting information about time spent cleaning/gardening.

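### Androgen profile is named a within-subjects factor, but each woman has only one androgen class, so the extended ANOVA cannot be fitted as stated

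*Protocol article*

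**What the plan says.** The Data analysis section of the protocol article first sets out a two-factor mixed ANOVA and gives the factors their correct roles: "The within-subjects factor is time, and the between-subjects factor is group". It then adds androgen profile. Using free testosterone, "all participants will be categorised by androgen profile as normo-androgenic or hyper-androgenic based on laboratory cut-off values". In the extended model, "time and androgen profile will be the within-subjects factors and group will be the between-subject factor". The section adds that "Partial eta squared will be presented" and names SPSS as the software.

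Under Study design, "Outcomes will be measured pre- and post- intervention", so each woman contributes two values per outcome. The planned size is 51, with 17 per group.

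The aims at the end of the Background include judging the use of partitioning the data by androgen profile. The Discussion lists this among the strengths and says that "partitioning data by androgen profile will highlight differences in normo- and hyper-androgenic cardiometabolic profiles". It also says that the study should supply effect sizes for planning the full-scale trial.

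**The concern.** A within-subjects factor is one at whose every level the same woman is observed. Time is such a factor. Androgen profile is not, because a woman is either normo-androgenic or hyper-androgenic. The two adjacent sentences in Data analysis are therefore incompatible. The Discussion describes a comparison between women, which agrees with the classification and not with the factor role. Nothing else in the article corrects the role. The article itself fixes it, so this is not a detail left to an analysis plan.

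At stake is the analysis that serves the androgen-profile aim. The stated model has no valid fit, so whoever runs it must depart from the published plan. Some departures are correct, but others test a difference between women against an error term that is too small.

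**Working it through.** **Inputs from the protocol article.** Three groups of 17, two visits, two androgen classes, one class per woman. The plan's own total reproduces: 3 × 17 = 51.

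**Assumptions not in the article.** Two-sided alpha 0.05; no true androgen effect; hyper-androgenic share 0.3 to 0.7 in each group; equal variances at the two visits; pre-post correlation ρ, shown over a range; no dropout.

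**1. Can the stated model be fitted?**
- Crossing time (2) with androgen profile (2) within women needs 2 × 2 = 4 cells per woman. Each woman fills 2, both in her own class. Women with all four cells: 0 of 51.
- With one indicator per woman, the design matrix has rank 51. The androgen column is the sum of the indicators of the hyper-androgenic women, so the rank stays 51 when it is added. No within-woman androgen contrast exists.
- The article does not say which visit's free testosterone defines the class. If women were reclassified at each visit, each would still have one class per visit and fill 2 of 4 cells.

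**2. The model with the role corrected.** With group (3) and androgen profile (2) between women and time within, there are six between-women cells. Error df = 51 − 6 = 45 in both strata. Simulated type I error for the androgen main effect (20,000 runs per setting) is 0.048 to 0.053.

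**3. The androgen main effect on a wrong error term.** Per unit variance, the mean square for a between-women effect has expectation 1 + ρ under the null. The within-women mean square has expectation 1 − ρ.

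*Within-women error (45 df).* F is inflated by (1 + ρ)/(1 − ρ). Type I error = P(F(1,45) > 4.06 × (1 − ρ)/(1 + ρ)).

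| ρ | inflation of F | type I error |
|---|---|---|
| 0 | 1.0 | 0.05 |
| 0.3 | 1.86 | 0.15 |
| 0.5 | 3.0 | 0.25 |
| 0.6 | 4.0 | 0.32 |
| 0.7 | 5.67 | 0.40 |
| 0.9 | 19.0 | 0.65 |

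Simulation at ρ = 0, 0.3, 0.5, 0.7 and 0.9 agrees to within 0.01, whatever the hyper-androgenic share.

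*Naive pooled error (subject left out of the model, 45 + 45 = 90 df).* The pooled mean square has expectation [(1 + ρ) + (1 − ρ)]/2 = 1, so F is inflated by 1 + ρ. The approximation P(F(1,90) > 3.95/(1 + ρ)) gives 0.11, 0.12 and 0.13 at ρ = 0.5, 0.6 and 0.7. A simulation of 8,000 runs with 12 and 5 women per arm gave 0.11, 0.12 and 0.14.

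**4. Androgen by group.** This term has 2 df and the same inflation of F, so its error rate is higher. P(F(2,45) > 3.20/3.0) = 0.35 and P(F(2,45) > 3.20/5.67) = 0.57 on the within-women error. On the pooled error, P(F(2,90) > 3.10/1.5) = 0.13 and P(F(2,90) > 3.10/1.7) = 0.17.

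**5. Partial eta squared** equals F·df1/(F·df1 + df2). Take a correct F of 1 on 1 and 45 df: 1/46 = 0.022. On the within-women error at ρ = 0.5 it becomes 3/(3 + 45) = 0.063, and at ρ = 0.7 it becomes 5.67/50.67 = 0.112. On the pooled error it falls slightly, to 1.5/91.5 = 0.016 at ρ = 0.5, because the error df double. It is too large only on the within-women error.

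**The case against.** The strongest reply is that this is a wording slip that would reveal itself. The plan names SPSS. A repeated-measures layout there leaves two of four columns empty for every woman, so the first run would fail and the analyst would move androgen profile to the between-subjects side, as the Discussion already implies. That is a likely course, and it limits the harm. It does not make the published rule right, and the correction would be an unrecorded departure from it.

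A reader might infer that the analysis must end either in no result or in a far too significant one, with a false-positive rate of 25% to 40%. The article does not support this. It describes no route that puts androgen profile on the within-women error. Other fits behave differently: with subject as a fixed effect androgen is aliased and there is no test; with a random intercept the between-women variance enters the test; with subject left out the rate is about 11% to 14%.

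A reader might also infer that the whole androgen analysis is invalid. Time by androgen, and time by androgen by group, belong in the within-women stratum. They address whether the interventions act differently by androgen profile, and they are sound once the role is corrected.

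Nor does the within-subjects label show that women will be reclassified after the intervention. The article is silent on which visit is used, and silence there is not an error.

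The reply is also right that the analysis is secondary and exploratory, and that the section carries a caveat for all results. That caveat concerns low power, however, and does not cover a model that cannot be fitted.

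**Conclusion.** The point holds. The factor role is wrong as written and the extended model cannot be fitted as stated. This conclusion needs no assumption beyond one androgen class per woman at a time.

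The false-positive figures are conditional. They apply to the androgen main effect, and in larger measure to androgen by group, and only if an analyst chooses an error term that leaves out or dilutes the between-women variance. They rest on an assumed correlation of 0.5 to 0.7 and on 51 completers. With ρ = 0 there is no inflation. Since the Withdrawals section limits analysis to completers, the actual error df would be below 45 after any dropout.

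Severity is moderate. A named aim and a claimed strength depend on this analysis. The primary feasibility outcomes, the main group by time ANOVA and the standard deviation of oxidised LDL do not.

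**What to change.** In Data analysis, replace the sentence on factor roles. It should say that androgen profile, classified from the baseline free-testosterone sample, is entered with group as a between-subjects factor, and that time is the only within-subjects factor.

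Naming the baseline sample keeps the classification independent of the intervention, since testosterone is itself listed as a secondary outcome in the Abstract. For the same reason, add that this factor is not used when free testosterone is the dependent variable, because it would then be a dichotomised form of the outcome.

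The cost is two sentences. No new data, visits or participants are needed.
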